## Abstract

**Background:**

Enteral nutrition is part of the treatment of critically ill patients. Administration of enteral nutrition may be associated with signs of intolerance, such as high gastric residual volumes, diarrhea, and vomiting. Clinical trials regarding the effects of the mode of administration of enteral nutrition on the occurrence of these complications have yielded conflicting results. This trial aims to investigate whether the mode of administration of enteral nutrition affects the time to reach nutritional targets, intolerance, and complications.

**Methods:**

COINN is a randomized, monocentric study for critically ill adult patients receiving enteral nutrition. Patients will be randomly assigned to two groups receiving (1) continuous or (2) intermittent administration of enteral nutrition. Enhancement of enteral nutrition will depend on signs of tolerance, mainly the gastric residual volume. The primary outcome will be the time to reach the energetic target. Secondary outcomes will be the time to reach the protein target, tolerance, complications, hospital and ICU lengths of stay, and 28-day mortality.

**Discussion:**

This trial aims to evaluate whether the mode of application of enteral nutrition affects the time to reach nutritional targets, signs of intolerance, and complications.

**Trial registration:**

ClinicalTrials.gov NCT03573453. Registered on 29 June 2018

## Introduction

### Background and rationale {6a}

Gastric enteral nutrition (EN) is commonly used in critically ill patients who cannot be fed orally [1, 2]. It can be performed with a continuous infusion or the administration of several boluses via a gastric tube. Continuous feeding consists of nutritional infusion at a constant rate. Intermittent nutrition involves administration of a bolus volume delivered over 15–40 min multiple times per day [3]. The rate of continuous infusion or the volume of the bolus is set to meet the daily energetic target. EN begins with the administration of a small amount of nutrition. If the EN is tolerated well, the amount of administered nutrition is increased until the target energy is reached. When signs of intolerance are recognized, the amount of administered nutrition is decreased; thus, the tolerance toward EN determines the time to reach the estimated energetic target—the primary outcome of this study. Both methods have advantages and disadvantages. Continuous administration of nutrients is unphysiologic, does not promote anabolism, and is associated with metabolic complications [4]. However, continuous administration is also associated with fewer gastrointestinal or respiratory complications, and meeting the nutritional targets earlier [5]. Intermittent feeding is physiologic and can promote proteosynthesis. However, it leads to high gastric residual volumes (GRVs) and higher occurrence of diarrhea and aspiration [6]. Studies investigating the effects of the mode of administration on the occurrence of complications and other outcomes have yielded conflicting results [6–9]. The authors of a systematic review of the effectiveness of continuous versus intermittent enteral nutrition have been unable to affirm recommendations for one method over the other [10]. The new guidelines of the European Society for Parenteral and Enteral Nutrition (ESPEN) on clinical nutrition in intensive care units recommend the use of continuous rather than bolus EN. However, the authors assumed that evidence on this issue is very limited, that bolus and continuous feeding are similar in achievement of nutritional targets without either increasing the rate of adverse effects, and that bolus feeding may be a greater stimulus for protein synthesis [11]. On the basis of current knowledge, a clear recommendation for a preferred method of administration of enteral feeding cannot be made [12, 13]. The aim of this study is to determine whether any difference exists in the time to reach the energetic target between two tolerance-driven modes of administration of EN in critically ill adult patients.

## Objectives {7}

The primary study objective is to compare continuous and intermittent modes of application of enteral feeding on the time to reach an energetic target in critically ill adult patients.

Key secondary objectives are to determine the effects of the mode of administration of enteral feeding on the time to reach the protein target, the gastrointestinal tolerance (on the basis of assessment of GRV), vomiting, diarrhea, and the need for postpyloric nutrition. Other secondary objectives are complications of enteral feeding, as assessed by the incidence of aspiration and ventilator-associated pneumonia (VAP).

## Trial design {8}

The COINN trial is designed as a prospective monocentric explorative trial with two parallel arms. The primary endpoint is the time to reach the energetic target in critically ill adult patients on enteral feeding. Block randomization with a 1:1 allocation will be performed.

## Methods: participants, interventions, and outcomes

### Study setting {9}

The COINN trial is currently ongoing in four intensive care units (ICUs) at one academic hospital in the Czech Republic.

### Eligibility criteria {10}

All patients admitted to the ICU are screened for the inclusion criteria. After informed consent is obtained, each patient is randomized to one of the trial arms. The randomization occurs before EN is started.

The inclusion criteria are as follows:
Age 18–80 yearsIndication of EN with a nasogastric or an orogastric tubeNutrition Risk in the Critically Ill (mNUTRIC) score ≥ 5Body mass index 18–50Mechanical ventilation expected for at least 72 h

Patients meeting any of the following criteria are excluded:
Upper gastrointestinal tract surgery in previous medical historyBowel obstructionBowel ischemiaAcute pancreatitisSevere diarrhea (> 1 L/24 h)Gastrointestinal bleedingShort bowel syndromeMalabsorption syndrome in previous medical historyOngoing EN on admission to ICU

### Who will take informed consent? {26a}

A trained study investigator will describe the study to patients or to authorized surrogates if applicable. Patients (or authorized surrogates) will also receive information sheets. The study investigator will discuss the study with patients (or authorized surrogates) in light of the information provided in the information sheets. The study investigator will obtain written consent from patients (or authorized surrogates) willing to participate in the trial. In the case of patients’ inability to consent because of a medical condition, the ability to participate in the trial will be assessed by a medical council consisting of one independent physician informed about the study details and one study investigator.

### Additional consent provisions for collection and use of participant data and biological specimens {26b}

Not applicable. Ancillary studies using participant data and biological specimens are not planned.

## Interventions

### Explanation for the choice of comparators {6b}

EN can be administered as separate bolus doses several times per day or as a continuous infusion over a long period of time. Continuous administration is favored by current ESPEN guidelines and will serve as the comparator for the intervention of intermittent feeding.

### Intervention description {11a}

The position of the gastric tube will be verified by measurement of gastric pH or abdominal X-ray. Commercial isocaloric formula with a high content of whey-based protein will be used. To eliminate the effects of formula composition on primary and secondary outcomes of the study, the same enteral formula will be used in all patients included in both study arms. Energetic and protein targets will be estimated according to current guidelines, on the basis of body mass index (BMI) and actual body weight (ABW), as summarized in Table 1 [1]. The energy and protein targets will be determined by the study investigator. The study investigator will provide information to the nurse and attending physician regarding the arm of the study to which the patient was assigned, the time of initiation of EN, and the target rate and bolus volume.

Administration of EN begins no earlier than 6 am and no later than 6 pm if signs of intolerance are absent (see below) and the GRV is below 500 mL. Otherwise, the start of EN will be postponed to the time of the next GRV measurement.

EN will be administered in the first arm (CONT) with continuous infusion via an enteral pump with an infusion time of 18 h per day. During the infusion, the patient will be in a 30–40° head-up position. The initial rate of infusion will be set to 25 mL/h and gradually increased every 4 h according to clinical signs of intolerance and GRV measurements. Signs of intolerance will be considered if abdominal distension or pain, vomiting, or diarrhea occur, and if the GRV exceeds 500 mL.

The rate of infusion will be increased according to tolerance and GRV. If there is no sign of intolerance, and the GRV is < 250 mL in two consecutive measurements, the rate will be increased by 25 mL/h until the target rate is reached. If signs of intolerance are absent, and the GRV is 250–500 mL, the current rate will remain unchanged. If intolerance signs are observed, or the GRV is > 500 mL, the rate will be decreased to half until the next assessment of tolerance and GRV.

The daily dose of EN will be divided in the second arm (INT) into six portions administered in 4-h intervals via an enteral pump. The rate of the enteral pump will depend on the volume of the bolus. To avoid sudden gastric distension, the rate will increase with increasing bolus volume [4]. The rates of the enteral pump for particular volumes of EN are summarized in Table 2.

During the infusion of EN, the patient will be in a 30–40° head-up position. After the administration is finished, the gastric tube will be rinsed with 20 mL of water. The initial volume of the bolus will be 80 mL and will be gradually increased every 4 h according to clinical signs of intolerance and GRV measurements. Signs of intolerance will be considered as abdominal distension or pain, vomiting, diarrhea, and a GRV exceeding 500 mL.

The rate of infusion will be increased according to tolerance and GRV. If there is no sign of intolerance and the GRV is < 250 mL in two consecutive measurements, the volume will be increased by 80 mL/h until the target volume is reached. If intolerance signs are absent and the GRV is 250–500 mL, the current volume of the bolus will remain unchanged. If intolerance signs or a GRV > 500 mL is observed, the volume will be decreased to half until the next assessment of tolerance and GRV.

Measurement of GRV will be performed throughout the entire study period (days 1–5) in 4-h intervals with a 150-mL syringe used for aspiration of gastric content. Volumes lower than 150 mL will be returned to the stomach, and larger amounts will be discarded.

**Table 1 Tab1:** Energy and protein targets

BMI	Energy	BMI	Protein
< 30	25–30 kcal/kg of ABW/24 h	< 30	1.2–2 g/kg ABW/24 h
30–50	11–14 kcal/kg of ABW/24 h	30–40	2 g/kg ABW/24 h
–	–	> 40	2–2.5 g/kg ABW/24 h

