### Outcomes {12}

The primary outcome of the trial is the time from the beginning of the administration of EN to the time at which at least 80% of the target energy is delivered. This will be reported as the day of EN administration. The Kaplan-Meier time-to-event analysis will be used for the analysis of the primary outcome.

Secondary outcomes:
Time from the beginning of the administration of EN to the time at which at least 80% of the target protein dose is delivered. This will be reported as the day of EN administration. The Kaplan-Meier time-to-event method of analysis will be used for the analysis of this secondary outcome.Achievement of the energetic target. This outcome will be aggregated as the proportion of patients who achieve the energetic target during the study period.Tolerance of EN GRV will be aggregated as the proportion with GRV < 250 mL, 250–500 mL, and > 500 mL. Episodes of vomiting will be aggregated as the proportion of patients with any number of episodes of vomiting. Diarrhea stools will be aggregated as the proportion of patients with diarrhea stool > 1 L/day. The need for postpyloric nutrition will be aggregated as the proportion of patients with this need.Incidence of complications of EN. The number of aspiration episodes will be aggregated as the proportion of patients with any number of episodes of aspiration. VAP will be aggregated as the proportion of patients with confirmed VAP.Total serum protein, albumin, and prealbumin concentrations on days 1 and 5. Serum concentrations of protein, albumin, and prealbumin will be aggregated as the mean.ICU and hospital length of stay. ICU and hospital length of stay will be aggregated as the mean. The day of admission and day of discharge will be counted as 1 day.The 28-day mortality will be evaluated with a Kaplan-Meier curve.

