#### Primary outcome

The time to reach the energetic target will be defined as the number of days from the beginning of the administration of EN until the day at which at least 80% of the planned EN is administered. The trial investigator will estimate the amount of EN administered by analyzing medical records in which the volume of EN is documented according to institutional standards.

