#### Secondary outcomes

The time to reach the protein target will be defined as the number of days from the beginning of the administration of EN to the day at which at least 80% of the planned protein administration has occurred. The trial investigator will estimate that day by analyzing the medical records.

GRVs, episodes of vomiting, the number and volume of diarrhea stools, and the need for postpyloric nutrition will be documented in the medical records and entered in the eCRF by the trial investigator. Diarrhea will be defined as passing of loose stools three or more times per day. The number and volume of stools will be documented in the medical records. Volumes of diarrhea stools exceeding 1 L/day will be reported.

Aspiration of EN is defined as the presence of EN in the airway of the patient. It will be assessed by a nurse during standard airway care and documented in the medical records. The number of aspiration episodes and the incidence of VAP will be entered in the eCRF by the study investigator. Total serum protein, albumin, and prealbumin concentrations on days 1 and 5 will be obtained from the electronic medical records and entered in the eCRF by the study investigator. The ICU and hospital length of stay will be entered in the eCRF by the study investigator after analysis of the medical records. The information on whether the patient is alive or dead on day 28 will be obtained by telephone.

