To promote EN tolerance, prokinetics will be used under the circumstances described in the “Relevant concomitant care permitted or prohibited during the trial {11d}” section of this protocol. Erythromycin or metoclopramide can be used. Both drugs are effective in decreasing feeding intolerance without increasing the rates of diarrhea and significant arrhythmias [23]. Metoclopramide has the same effectiveness regardless of the mode of administration, and the choice of a particular agent and mode of administration will be the responsibility of the attending physician [24]..

Regarding the primary outcome, the time to reach the energy target has been compared in two studies [6, 8]. After a detailed review of the study protocols, we have found that in both these studies, the increments of EN in the intermittent and continuous arm were set differently. In the case of optimal tolerance of EN, the energy target would have been reached at different time points, although the EN would have been started simultaneously in the bolus or continuous arm. Therefore, comparison of EN administration modes is problematic. In our study, we set the increments of EN so that the energy target is reached at the same time point regardless of whether EN is administered continuously or as a bolus. Therefore, both modes of EN administration are comparable regarding the primary outcome.

Aspiration of EN is a complication of EN administration. Objectively estimating aspiration is difficult. The method of coloring EN has been used in some studies. However, this method is currently not recommended for identification of aspiration because of potential adverse metabolic effects of the dye [25–27].

Aspiration of EN will be identified and noted in the medical record by nursing staff during standard airway care. This method of identification of EN aspiration is highly subjective and may be a potential source of bias.

In conclusion, we believe that this randomized trial will provide additional information regarding whether continuous or bolus feeding is associated with any differences in the tolerance and complication rate.

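### With one formula capped at the energy target and no supplement mentioned, patients with BMI 30 or more cannot reach 80% of their protein target unless the formula holds at least 114 to 182 g protein per 1000 kcal

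*Protocol article*

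**What the plan says.** Eligibility admits patients with BMI from 18 to 50. Table 1 (Intervention description {11a}) sets these daily targets per kg of actual body weight:

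- BMI below 30: energy 25–30 kcal, protein 1.2–2 g.
- BMI 30–50: energy "11–14 kcal/kg of ABW/24 h".
- BMI 30–40: protein 2 g. BMI above 40: protein 2–2.5 g.

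The same section says that "the same enteral formula will be used in all patients included in both study arms". It calls the formula isocaloric and rich in whey protein but gives no protein density. Background {6a} states the dosing rule: "The rate of continuous infusion or the volume of the bolus is set to meet the daily energetic target". Escalation in the intermittent arm continues "until the target volume is reached", and the continuous arm has the matching rule for its rate. The Discussion confirms what the steps aim at: "we set the increments of EN so that the energy target is reached at the same time point". The only timing given for parenteral nutrition is days 7–10, whereas Table 3 assesses the targets on days 1–5.

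The protein outcome is worded in two ways. Outcomes {12} counts to "the time at which at least 80% of the target protein dose is delivered". The data-collection text on secondary outcomes {18a} counts to "the day at which at least 80% of the planned protein administration has occurred". For energy, {18a} uses "at least 80% of the planned EN is administered".

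**The concern.** A single formula fixes the ratio of protein to energy for every patient. Table 1 asks for a much higher ratio at BMI 30 or more than below 30, because it cuts energy by about half and does not cut protein. If volume stops at the energy target, protein stops with it, and patients with BMI 30 or more may be unable to reach the 80% protein threshold however well they tolerate feeding.

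Time to the protein target is named first among the key secondary objectives in Objectives {7}. Patients who cannot have the event would be censored at day 5 in both arms for a reason unrelated to feeding mode. Attainment would fall, the Kaplan-Meier medians would move later, and an unstratified log-rank test would lose power.

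**Working it through.** The article gives neither a formula density nor an expected protein attainment, so there is no stated figure to reproduce. Steps 1 to 3 use Table 1; step 3 adds one assumed density.

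**1. Ratio implied by Table 1** (protein target ÷ energy target × 1000, in g per 1000 kcal)

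- BMI below 30: 1.2/30 = 40 up to 2/25 = 80.
- BMI 30 or more: 2/14 = 143 up to 2.5/11 = 227.

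The two ranges do not overlap.

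**2. Density needed for 80% of the protein target at 100% of the energy target** (0.8 × protein ÷ energy × 1000)

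| Protein (g/kg) | Energy (kcal/kg) | Density needed (g per 1000 kcal) |
|---|---|---|
| 2 | 14 | 114.3 |
| 2 | 11 | 145.5 |
| 2.5 | 14 | 142.9 |
| 2.5 | 11 | 181.8 |

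Below 114 g, every combination falls short of 80%. At 114.3 g, a patient with BMI below 30 at full energy would receive 0.1143 × 25 = 2.86 to 0.1143 × 30 = 3.43 g/kg, against a Table 1 upper value of 2 g/kg.

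**3. Attainment at an assumed 80 g per 1000 kcal**

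- Protein delivered: 0.08 × 11 = 0.88 to 0.08 × 14 = 1.12 g/kg.
- Against 2 g/kg: 44–56%. Against 2.5 g/kg: 35–45%.
- Shortfall to 80% of 2 g/kg (1.6 g/kg): 0.48–0.72 g/kg, or 48–72 g a day at 100 kg.
- Energy needed to deliver 1.6 g/kg: 1.6/0.08 = 20 kcal/kg, which is 143% (20/14) to 182% (20/11) of the energy target.

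Sensitivity to the assumed density, over all combinations: 40 g gives 18–28% of target, 60 g gives 26–42%, 100 g gives 44–70%.

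**4. Effect on the time-to-event analysis.** Let s be the share with BMI 30 or more, all of them without an event. Attainment in each arm is multiplied by (1 − s). The simulation below is an illustration. It takes 150 per arm, geometric daily event times with medians of day 2 and day 3 (the Sample size {14} hypothesis, which was made for energy), censoring at day 5, a two-sided 5% level and 6000 runs. It assumes that the log-rank test named for the primary outcome is also used here.

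| s | Day-5 attainment, two arms | Power, unstratified | Power, stratified by BMI |
|---|---|---|---|
| 0% | 82%, 69% | 86% | 86% |
| 15% | 70%, 58% | 64% | 80% |
| 25% | 62%, 51% | 52% | 75% |
| 40% | 49%, 41% | 34% | 66% |

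At s = 25% the medians become day 4 and day 5; at 40% neither is reached by day 5. With no true difference and s = 25%, rejection is 5.3% unstratified and 4.9% stratified, so the type I error is not inflated. With a smaller effect (day 2 v day 2.5, 4000 runs), power is 40% at s = 0, and 18% unstratified v 31% stratified at s = 25%.

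**5. BMI below 30.** One formula makes protein a rescaled energy measure here as well. At 80 g per 1000 kcal and a 1.2 g/kg target, 80% of protein is 0.96 g/kg, reached at 0.96/0.08 = 12 kcal/kg. That is 40–48% of the energy target. With a 2 g/kg target and 25 kcal/kg, both 80% thresholds fall together.

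**The case against.** Much of the opposing case is sound.

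- **Density.** A reader might take 35–56% as a ceiling set by the plan. It is not: no density is stated, and nothing forbids giving patients with BMI below 30 more than 2 g/kg. A formula between 80 and 114 g could give up to 56–80% in the best combination. That is still below the endpoint.
- **The 114 g threshold.** A reader might take it as sufficient for everyone. It suffices only at 14 kcal/kg with a 2 g/kg target; the other combinations need 143–182 g.
- **Supplements.** The article neither mentions nor excludes one, and a condensed article commonly leaves product details to the full protocol. The silence is therefore no fault in itself, and the conclusion must stay conditional on it.
- **Two wordings.** A reader might infer that {12} and {18a} contradict each other. The energy outcome varies in the same way, and planned may simply mean the investigator's target. Only if planned protein means the protein in the planned volume would the endpoint be reachable by all, and it would then duplicate the energy endpoint. This is a possible reading, not an established conflict.
- **Size.** The trial is described as explorative and claims no power for this outcome. The share with BMI 30 or more is not given. At a 5% share, simulated power is about 80% v 86% with none, so the loss could be small.
- **Remedy.** A stratum without events adds nothing, so the stratified test rests on patients with BMI below 30. That is true, but it still avoids the dilution.

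What remains is the incompatibility itself. Table 1, one formula, a cap at the energy target and the 80% threshold of {12} are all stated, and for BMI 30 or more they cannot be met together without a supplement or a density of at least 114–182 g per 1000 kcal.

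**Conclusion.** The point holds in conditional form. It rests on the {12} definition and on no protein being given outside the formula during days 1–5. The 114–182 g thresholds follow from Table 1 alone. The power figures also depend on an unstated BMI share, an effect size borrowed from the energy endpoint, and the assumed log-rank test.

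A reader might infer a biased comparison or a compromised primary outcome. The documents support neither: the limit applies equally in both randomised arms, and the energy target stays reachable at every BMI. The damage is loss of information and interpretability in one key secondary outcome. That merits correction before analysis, but it does not threaten the trial's main conclusion.

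**What to change.** Leave the Table 1 targets and patient care as they are.

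1. Use one definition in {12} and {18a}: the first day on which protein delivered from all enteral sources is at least 80% of the Table 1 target dose.
2. Stratify the log-rank test for this outcome by BMI below 30 v 30 or more, keeping all randomised patients.
3. Report daily protein delivered as a percentage of target on days 1–5, by BMI class and arm, as description.

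The cost is one definition and one analysis line, fixed before the data are analysed, possibly with a short amendment under {25}. BMI can be derived from the recorded height and weight, and EN volumes are already recorded. Supplement amounts, if any are given, would have to be added. The downside is that, without supplements, the time-to-event result is informed only by patients with BMI below 30, in whom it largely tracks the energy endpoint. The report should say so.

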### Sample size {14}

Studies focused on the primary target of our study are lacking. However, we have identified several studies comparing bolus and continuous administration of enteral feeding. These studies included small numbers of patients, were conducted in different patient populations, and did not assess the time to reach the nutritional targets as a primary outcome. However, for calculation of the sample size, we hypothesized a difference of 1 day between groups (target being reached on day 2 and day 3, respectively). The alpha was set to 5%, and the power was set to 80%. The estimated sample size was 122 patients per arm. To account for potential drop-out, we increased the sample size to 300 participants in total, with 150 patients in each study arm.

**Table 3 Tab3:** Participant timeline

	Study period							Follow-up
Time point	Screening	D0	D1	D2	D3	D4	D5	D28
Number of visits	1	2	3	4	5	6	7	8
Eligibility criteria	x							
Informed consent	x							
Allocation	x							
Demographic data		x						
APACHE II		x						
SOFA score		x						
Laboratory tests (total serum protein, albumin, prealbumin)		x					x	
Estimation of energy and protein target		x						
Administration of enteral nutrition			x	x	x	x	x	
Assessment of tolerance (diarrhea, vomiting, GRV, postpyloric nutrition)			x	x	x	x	x	
Assessment of complications			x	x	x	x	x	
Assessment of energetic and protein targets			x	x	x	x	x	
Assessment of hospital LOS, ICU LOS, and mortality								x

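### The energy target that forms the denominator of the primary endpoint is chosen from a 20% to 27% wide range, after allocation, by an unblinded investigator

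*Protocol article*

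**What the plan says.** All references are to the Protocol article.

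- **Endpoint.** Outcomes {12} counts time from the start of enteral nutrition (EN) "to the time at which at least 80% of the target energy is delivered". The Primary outcome part of {18a} counts days "until the day at which at least 80% of the planned EN is administered".
- **Target.** Table 1 gives energy as "25–30 kcal/kg of ABW/24 h" for BMI below 30 and "11–14 kcal/kg of ABW/24 h" for BMI 30–50. For protein, a secondary endpoint, it gives "1.2–2 g/kg ABW/24 h" for BMI below 30. On who chooses, {11a} says: "The energy and protein targets will be determined by the study investigator". It gives no rule for the point within the range.
- **Timing.** In Table 3, allocation is marked under Screening, and the row "Estimation of energy and protein target" is marked under D0, one visit later. {10} requires only that randomisation follow consent and precede EN.
- **Roles.** The study investigator randomises ({16c}) and tells ward staff the arm together with the target rate and bolus volume ({11a}). Study and treating staff are not blinded ({17a}). The trial investigator later works out the delivered amount from the medical records ({18a}).

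**The concern.** The event is a ratio reaching 80%. In an open trial, both parts of that ratio should be beyond the reach of anyone who knows the arm. Here the denominator is a judgement within a wide range, and on the article's schedule it is made once the arm is known. If the low end of the range is used more often in one arm, even unconsciously, patients in that arm face a lower threshold and tend to be counted as reaching the target earlier.

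The Discussion argues that the arms are comparable on the primary outcome because the feeding increments were matched. That argument also needs the targets to be comparable between arms, and nothing in the article secures this.

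**Working it through.** The plan gives no figure of its own for this point. The sample size of 122 per arm is used below only as a simulation setting and is not contested.

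**1. Width of the choice (Table 1)**
- BMI below 30: (30 − 25)/25 = 20.0% of the lower bound (5/30 = 16.7% of the upper).
- BMI 30–50: (14 − 11)/11 = 27.3% of the lower bound (3/14 = 21.4% of the upper).
- Protein, BMI below 30: (2 − 1.2)/1.2 = 66.7% of the lower bound.

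**2. Effect on the threshold**
- BMI below 30: 0.8 × 25 = 20 kcal/kg against 0.8 × 30 = 24 kcal/kg. Delivery of 20 kcal/kg is an event under the first target and 20/30 = 66.7%, no event, under the second.
- BMI 30–50: 0.8 × 11 = 8.8 kcal/kg against 0.8 × 14 = 11.2 kcal/kg. Delivery of 8.8 kcal/kg is 62.9% of the upper target.

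**3. Perfect tolerance (assumes 1 kcal/mL)**

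For a 60 kg patient, the targets are 1500 or 1800 kcal.
- Intermittent arm, a step at every 4-h check: 80 + 160 + 240 + 3 × 250 = 1230 mL (82.0%), against 80 + 160 + 240 + 3 × 300 = 1380 mL (76.7%). The event moves from day 1 to day 2.
- Intermittent arm, a step every 8 h, one reading of the rule requiring two consecutive gastric residual volume (GRV) measurements: 2 × (80 + 160 + 240) = 960 mL. This is 64.0% and 53.3%, so the event does not move.
- Continuous arm, 4-h steps over 18 h: 1100 mL (73.3%) and 1200 mL (66.7%), so the event does not move.

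Across six body weights, two arms and two step lengths (24 scenarios), the choice of end moved the event by one day in 4. The choice matters mainly when tolerance is incomplete.

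**4. Illustrative null simulation**

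The settings are 122 per arm, five days, BMI below 30, a two-sided 5% log-rank test and 2000 runs per cell. Both arms have the same assumed delivery curve: mean 11, 18, 22, 24.5 and 26 kcal/kg on days 1–5, capped at the target. Between-patient SD on the log scale is 0.2, 0.3 or 0.4. Only the share of patients given 25 rather than 30 kcal/kg differs by arm.

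| Low end used, by arm | Rejection rate (SD 0.2 / 0.3 / 0.4) | Difference in mean day |
|---|---|---|
| 50% v 50% | 4.7% / 4.7% / 5.1% | about 0 |
| 40% v 60% | 20.1% / 10.9% / 9.3% | 0.17 / 0.12 / 0.11 |
| 25% v 75% | 79.5% / 51.3% / 34.3% | 0.41 / 0.33 / 0.28 |
| 0% v 100% | 100% / 98.1% / 87.4% | 0.82 / 0.65 / 0.55 |

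The planned effect is 1 day ({14}). Discretion used equally in both arms leaves the type I error near 5%; unequal use inflates it.

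**The case against.** **Points that stand in part**
- *The order rests on the columns of Table 3.* BMI is an inclusion criterion and weight and height are measured on admission, yet demographic data also sit at D0, so the columns may not be a strict sequence. This is fair. Still, it is the only order the article gives, and no statement fixes the target first.
- *Investigator is a role, not one person, and another team member reviews each eCRF ({19}).* This is true. But that review is described as a data-quality step, and nobody in the role is blinded.
- *The full protocol may hold a rule for the point within the range.* It may. If so, the remedy is to cite it and confirm that it applies before allocation.

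**Stronger readings that the article does not support**
- *The choice alone is worth a full day.* The one-day move in the 60 kg example needs the intermittent arm and a step at every 4-h check. It occurred in only 4 of 24 perfect-tolerance scenarios.
- *A lower target brings an earlier event with feeding unchanged.* The target also caps the rate and the bolus, so it changes feeding too (1230 against 1380 mL above).
- *The two endpoint wordings are two different endpoints.* With a single isocaloric formula they coincide if planned EN means the full target volume, which is the natural reading. They part only if it means the current titration step or the fixed rate in {11d}. A wording correction is enough.
- *Discarded aspirate inflates the delivered amount.* Of aspirates, {11a} says smaller ones "will be returned to the stomach, and larger amounts will be discarded". That material is gastric content, not pure EN, so subtracting it would over-correct by an unknown amount.

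**Conclusion.** The point holds as an avoidable route to bias in the primary endpoint. The event threshold can differ by 20% (BMI below 30) or 27% (BMI 30–50) at the discretion of someone who, on the article's schedule, already knows the arm. The time to the protein target has the same weakness, with a range up to 67% wide.

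A reader might infer that the result will be biased, or biased toward one arm. The article supports neither. The simulated type I errors, 9% to 20% under a 40% v 60% imbalance, depend on an assumed delivery curve and an assumed imbalance. They show that a modest imbalance could matter, not that one exists. The conclusion also rests on Table 3 reflecting the actual order of events and on there being no rule elsewhere for the point within the range.

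**What to change.** 1. **Lock before allocation.** For all patients still to be randomised, require weight, height and the energy and protein targets to be entered and locked in the eCRF before the randomisation step opens, and amend Table 3 to match. The Trial status section reports 100 of 300 randomised, so at that date the lock would cover the remaining 200.
2. **One endpoint wording in {12} and {18a}.** Use the first day on which delivered EN energy is at least 80% of the locked full target. For patients enrolled before the change, use the target recorded at the time.
3. **Transparency and sensitivity.** Report the chosen kcal/kg by arm. For patients already enrolled, add a sensitivity analysis of the primary endpoint against a common kcal/kg threshold per BMI class, fixed before any look by arm. The threshold must be attainable under every target that Table 1 permits. For BMI 30–50, 80% of the upper bound (11.2 kcal/kg) would fail this, because a patient fed fully to 11 kcal/kg reaches only 11/14 = 78.6% of 14. For the same reason, one coefficient per class should not replace the recorded targets in the primary analysis. Because the target also caps delivery, this analysis reduces the problem for those patients but cannot fully remove it.

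The cost is an ordering check in an eCRF that already performs the randomisation, a short amendment and one extra analysis. Weight and height are already measured on admission. No feeding prescription changes, and no value within the ranges is proposed here.
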